## Abstract

**Background:**

In recent years there has been an increasing interest in MRI as a non-invasive diagnostic modality for the work-up of suspicious breast lesions. The additional value of Breast MRI lies mainly in its capacity to detect multicentric and multifocal disease, to detect invasive components in ductal carcinoma in situ lesions and to depict the tumor in a 3-dimensional image. Breast MRI therefore has the potential to improve the diagnosis and provide better preoperative staging and possibly surgical care in patients with breast cancer. The aim of our study is to assess whether performing contrast enhanced Breast MRI can reduce the number of surgical procedures due to better preoperative staging and whether a subgroup of women with suspicious nonpalpable breast lesions can be identified in which the combination of mammography, ultrasound and state-of-the-art contrast-enhanced Breast MRI can provide a definite diagnosis.

**Methods/Design:**

The MONET – study (***M***R mammography ***O***f ***N***onpalpable Br***E***ast ***T***umors) is a randomized controlled trial with diagnostic and therapeutic endpoints. We aim to include 500 patients with nonpalpable suspicious breast lesions who are referred for biopsy. With this number of patients, the expected 12% reduction in surgical procedures due to more accurate preoperative staging with Breast MRI can be detected with a high power (90%). The secondary outcome is the positive and negative predictive value of contrast enhanced Breast MRI. If the predictive values are deemed sufficiently close to those for large core biopsy then the latter, invasive, procedure could possibly be avoided in some women. The rationale, study design and the baseline characteristics of the first 100 included patients are described.

**Trial registration:**

Study protocol number NCT00302120

## Background

Breast cancer is the most frequently occurring malignant disease in women with a lifetime risk of 1 in every 8 – 9 women [1]. Like many other Western countries, the Netherlands launched a screening program for breast cancer and since 1998, all women between 50 and 75 years of age are offered biannual mammographic examination. This program reveals approximately 4000 suspicious, nonpalpable breast lesions each year in the Netherlands [2]. In clinical practice, another 3000 nonpalpable lesions are detected annually in women with a high genetic risk or a history of breast cancer [3]. Of all suspicious nonpalpable breast lesions, 10–55% of lesions turn out to be malignant (ductal carcinoma in situ or invasive carcinoma) after large core needle biopsy (LCNB) depending on the aggressiveness of the referral of patients which varies across countries [4]. Subsequently, these patients are scheduled for surgical removal of the malignant breast tumor. In a relatively high proportion of these patients (approximately 20–30%), several surgical procedures (re-excisions or conversions from lumpectomy towards mastectomy) are needed to achieve complete removal of the primary tumor. The reasons for this include unanticipated invasiveness, multifocality, axillary lymph node involvement or incomplete removal of the primary tumor [5]. A more accurate preoperative diagnosis could help to reduce the number of surgical procedures and invasive biopsies.

In recent years there has been an increasing interest in MRI as a non-invasive diagnostic modality for further characterizing suspicious breast lesions detected with mammography or ultrasound. In a recent meta-analysis, we found that the sensitivity and specificity of MRI to diagnose breast cancer is 0.90 (95% CI 0.88 – 0.92) and 0.72 (95% CI 0.67 – 0.77) respectively [6]. Although these results are promising, the diagnostic performance is not sufficiently high to obviate LCNB for a definitive diagnosis. We believe that the additional value of MRI of the breast lies mainly in its capacity to detect multicentric, multifocal and bilateral disease [7-13], to detect invasive components in ductal carcinoma in situ (DCIS) lesions [8,11,13,14], to depict the tumor in a 3-dimensional image [8,11,14,15] and to depict breast cancer in dense breast tissue [15,16]. Breast MRI therefore has the potential to improve the diagnosis of invasive breast cancer and the preoperative staging of the breast. To assess this potential, we started a randomized clinical trials (the MONET – study: ***M***R mammography ***O***f ***N***onpalpable br***E***ast ***T***umors, clinical trials: study protocol number NCT00302120 [17]). The purpose of this trial is to assess whether performing contrast enhanced Breast MRI can reduce the number of invasive procedures in patients with nonpalpable suspicious breast lesions. Therefore, we will evaluate whether performing preoperative contrast-enhanced Breast MRI in women referred for surgical treatment, reduces the number of surgical procedures. Furthermore, we will assess whether a subgroup of women with suspicious nonpalpable breast lesions can be identified in which the combination of mammography, ultrasound and state-of-the-art contrast-enhanced Breast MRI can provide a definite diagnosis. If Breast MRI in addition to mammography and ultrasound will turn out to have a high positive predictive value, biopsies could possibly be prevented in some women in the future.

## Study design and methods

### Subjects

Women with nonpalpable suspicious breast lesions (BI-RADS category 3, 4, or 5) detected on mammography or breast ultrasound, who are referred for histological analysis of the lesion, are eligible for the study. Exclusion criteria are age below 18 or above 75 years, breast surgery or radiation therapy of the breast less than 9 months prior to inclusion, pregnancy or lactation, claustrophobia, severe obesity (> 130 kg), general contraindications for MRI (i.e. cardiac pacemaker, metal implants or history of severe allergic reaction after administration of contrast agent), inability to maintain in prone position for one hour, medically unstable patients and severe coagulopathies or use of anti-coagulants that cannot be discontinued. Written informed consent will be obtained from all patients. The study has been approved by the ethical boards of the participating hospitals.

### Study design

The MONET – study is a randomized controlled trial. Patients will be recruited in 3 hospitals: two large community teaching hospitals and one University Medical Center. In all participating centers, Breast MRI is not part of routine clinical practice in the work-up of patients with suspicious nonpalpable breast lesions. We aim to include a total of 500 patients with nonpalpable, mammographically suspicious breast lesions who are referred for biopsy. After giving informed consent, patients will be randomized in the control group or the MRI group. Patients in the control group (n = 250) will undergo routine medical care. This includes mammography, ultrasound, and the lesion is sampled by means of large core needle biopsy. In case of malignancy (DCIS or invasive carcinoma), the lesion is surgically removed. The MRI group (n = 250) will undergo routine clinical care and in addition, contrast enhanced Breast MRI in the University Medical Center prior to the large core needle biopsy. The MRI scan will be performed within one week after mammography and before LCNB which will be performed within one week after MRI to avoid a diagnostic delay.

### Randomization

Randomization is stratified by hospital. In each hospital, randomization within strata is blocked with a fixed block size. Randomization is performed by an independent trial center. If a patient meets the inclusion criteria and has provided informed consent, the physician contacts the trial center by phone. The trial center will perform the randomization of the patients.

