## Statistical considerations

### Sample size

The statistical power of the study was calculated for the primary endpoint (reduction in the number of surgical procedures). Based on data of previous studies on nonpalpable suspicious breast lesions and literature, we expect 23% of patients with suspicious nonpalpable breast lesions to require more than one surgical procedure to remove all tumorous tissue [19,22-26]. This number includes patients with mammographically occult multifocal and multicentric disease (8%), patients who require a surgical re-excision because all tumorous tissue could not be removed in one procedure (10%) and patients with a DCIS lesion with a mammographically occult invasive component in the surgical specimen (5%) [19,22-26]. We expect that additional contrast enhanced Breast MRI will reduce this number to 11% due to earlier detection of invasiveness, multifocality and muticentricity and a better 3D depiction of the tumor. With a statistical power of 90% to detect this 12% reduction as significant (p < 0.05, two-sided), we will require 250 women in the control group and 250 women in the MRI group (95% confidence interval 6% to 19%). We consider a reduction larger than 5% clinically relevant.

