## Preliminary results

Between January 2006 and November 2006, 174 patients were eligible for the MONET – study. 108 patients were included in the study (recruitment rate 62%). The reasons for non-participation are listed in Table 1. Eight patients were excluded after randomization (no available histology (n = 5), unanticipated obesity (n = 1), technical failure of MR scanner (n = 1), age over 75 years (n = 1)). Three of the excluded patients were randomized in the control group and 5 in the MRI group. The characteristics of the 100 patients included so far in the MONET – study are summarized in Table 2. The mean age was 56.1 years (range 39.9 – 75.0 years). In these patients, a total of 109 lesions were detected: 108 lesions were detected on mammography and 1 lesion on ultrasound imaging. The majority of the lesions were microcalcifications and classified as BI-RADS 3 or 4. The histological diagnosis of the lesions included 2 non-representative, 9 normal breast tissue, 62 benign lesions, 21 non-invasive carcinomas and 19 invasive carcinomas. So, 35.4% of lesions turned out to be malignant (non-invasive and invasive) after LCNB. Forty-five patients were randomized into the MRI group and 55 into the control group.

**Table 1 T1:** Reasons for non-participation

**Reason non-participation**	**Number of patients (%)**
Unable to lie in prone position	1 (1.5%)
Metal implants	6 (9.0%)
Severe obesity	1 (1.5%)
Claustrophobia	16 (24.0%)
Geographical distance from teaching hospital to MRI too long	18 (27.0%)
Clinical indication for MRI of the breast	1 (1.5%)
Personal reasons	23 (35.0%)
**Total**	**66**

**Table 2 T2:** Characteristics of the first 100 patients included in the MONET – study

n	**100**
Referred from University Medical Center	**30**
Mean age (*range*)	**56.1 **(*39.9 – 75.0*)
Number of lesions detected on mammography	**108**
*density only*	*41*
*microcalcifications only*	*54*
*both*	*9*
*other*	*2*
*unknown*	*2*
BI-RADS classification mammography	
*3*	*45*
*4*	*47*
*5*	*11*
*unknown*	*5*
Number of lesions detected on ultrasound (*mammographically occult lesions*)	**1**
BI-RADS classification ultrasound	
*3*	*1*
*4*	*-*
*5*	*-*
*unknown*	*-*
Diagnosis LCNB	**113***
*non-representative*	*2 (1.7%)*
*normal breast tissue*	*9 (8.0%)*
*benign*	*62 (54.9%)*
*non-invasive carcinoma*	*21 (18.6%)*
*invasive carcinoma*	*19 (16.8%)*

* 4 lesions were sampled twice because of inconclusive results

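### A fixed block size within each hospital lets sites deduce some coming allocations in this open trial; separately, the 50:58 split implied by the preliminary results needs reconciling with the block scheme.

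*Protocol article*

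**What the plan says.** All quotes are from the protocol article.

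- **Scheme (Randomization).** "Randomization is stratified by hospital", and "In each hospital, randomization within strata is blocked with a fixed block size". The size of the block is not given, and no stratum other than hospital is named.
- **Concealment (Randomization).** "Randomization is performed by an independent trial center". The order of events is also stated: "If a patient meets the inclusion criteria and has provided informed consent, the physician contacts the trial center by phone".
- **Number of hospitals (Study design).** "Patients will be recruited in 3 hospitals: two large community teaching hospitals and one University Medical Center".
- **Ratio (Sample size).** "we will require 250 women in the control group and 250 women in the MRI group", which implies 1:1.
- **Visibility of the arm.** Only the MRI group has the extra scan, at the University Medical Center (Study design), and the surgeon is shown the images (Surgery).
- **Counts to November 2006 (Preliminary results).** 108 patients were included and eight were excluded after randomization: "Three of the excluded patients were randomized in the control group and 5 in the MRI group". For the 100 who remained: "Forty-five patients were randomized into the MRI group and 55 into the control group".

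**The concern.** There are two separate matters.

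**Predictability.** When the arm is visible after each allocation and hospital is the only stratum, a hospital's own enrolment history is its whole allocation sequence. A block of constant size must finish balanced, so its last places are sometimes forced. Hiding the list does not prevent that deduction. A physician who expects a particular arm could then, knowingly or not, let the expectation affect whom to approach or when to call. The primary outcome counts biopsies and operations, which depend on clinicians' decisions in an open trial. Unbiased entry is therefore an important protection for the comparison.

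**The split.** Adding the post-randomization exclusions back gives arms that differ by 8. Blocking within three hospitals is meant to keep the overall difference small, so the reported counts invite the question of which scheme produced them.

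**Working it through.** **1. Arm totals at randomization** (counts from Preliminary results)

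- MRI: 45 + 5 = 50
- Control: 55 + 3 = 58
- Total: 50 + 58 = 108, which agrees with the stated 108. Difference: 58 − 50 = 8.
- Still to enrol: 500 − 108 = 392.

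**2. Can blocks give a difference of 8?** Assume 1:1 allocation, three strata and one common block size b. Completed blocks are balanced, so all imbalance comes from the one open block in each hospital, at most b/2 per hospital and 3b/2 in all.

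- b = 2: bound 3, below 8. Impossible.
- b = 4: bound 6, below 8. Impossible.
- b = 6: bound 9, so the bound alone does not exclude 8. A total of 8 needs hospital imbalances of 3, 3 and 2. An imbalance of 3 needs 3 patients in the open block; an imbalance of 2 needs 2 or 4. The open blocks then hold 3 + 3 + 2 = 8 or 3 + 3 + 4 = 10 patients, so the total would leave remainder 2 or 4 on division by 6. But 108 = 18 × 6 leaves remainder 0. Impossible.

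Enumerating every division of 108 among three hospitals gives largest attainable differences of 2, 4 and 6 for blocks of 2, 4 and 6. A block of 8 is the smallest even size that can give 50:58.

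**3. How likely is it with larger blocks?** The article does not give hospital totals for the 108 (Table 2 gives only 30 of the 100 retained patients as University Medical Center referrals). The table shows the probability of a difference of 8 or more in either direction. The maximum is taken over all divisions of 108. The typical value assumes 30 to 38 patients from the University Medical Center and a random division of the rest.

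| Block | Maximum | Typical |
|---|---|---|
| 8 | 0.5% | 0.1% |
| 10 | 1.1% | 0.3% |
| 12 | 1.5% | 0.5% |
| 20 | 7.4% | 3.5% |

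Under simple randomization the same probability is 50%.

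**4. Predictability for someone who knows the block size.** Write b = 2m. The share of allocations that are certain is 1/(m + 1). Someone who always guesses the arm that is behind in the block is right in a share [m + (4^m / C(2m, m) − 1)/2] / (2m) of cases. Worked for b = 8 (m = 4): certain 1/5 = 20%; guessed [4 + (256/70 − 1)/2]/8 = (4 + 1.329)/8 = 67%.

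| Block | Certain | Guessed correctly |
|---|---|---|
| 4 | 33% | 71% |
| 6 | 25% | 68% |
| 8 | 20% | 67% |
| 12 | 14% | 64% |
| 20 | 9% | 62% |

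Chance is 50%.

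**5. Effect of relaxing the assumptions.**

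- *Hospital-specific block sizes.* Blocks of 6, 6 and 4 in hospitals with 33, 45 and 30 patients (sum 108) leave 3, 3 and 2 in the open blocks. A difference of 3 + 3 + 2 = 8 is then attainable, though very rare.
- *More than three strata.* With four or more, blocks of 4 or 6 can also give 50:58.

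**The case against.** Fixed blocks within hospital, allocated by telephone from an independent center after eligibility and consent, are a common and accepted design. The telephone service is recognised allocation concealment. The predictability figures assume that someone at the site knows or works out the block size, and nothing in the article says that anyone does. This stands: it limits the point to a risk that is cheap to remove.

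The article never gives the block size, so 50:58 contradicts nothing it prints. Blocks of 8 or more fit both sections, and so would sizes that differ by hospital. The words about strata within each hospital could also be read as allowing further strata. This stands too, and it makes the split a query rather than a proven error.

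The two parts also pull in different directions. If one common block size was used in three strata, the split rules out 4 and 6, which are among the most predictable sizes. The relevant figures would then be those for 8 and above. They are lower, but at 20% certain for 8 and 14% for 12 they are not negligible.

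A reader might go further and infer that the described scheme is not the one in use, or that enrolment has been steered. The documents support neither. A large block or a miscount would explain the split without any selection bias. Table 1 gives women's reasons for not taking part but does not link them to an expected arm.

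**Conclusion.** The point holds in two limited parts.

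**Predictability.** A fixed block in an open trial with hospital as the only named stratum leaves an avoidable share of allocations deducible: 20% certain and 67% guessable for a block of 8, 14% and 64% for 12, and 33% and 71% for 4. These figures assume 1:1 blocks and a site that knows or has inferred the size. No breach is shown.

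**The split.** On the plain reading (1:1, three hospital strata, one common block size, all 108 randomized), a difference of 8 cannot come from blocks of 2, 4 or 6. It has a probability of at most 0.5% with 8, 1.5% with 12 and 7.4% with 20. The exclusion of 6 depends on the total being exactly 108. Larger or hospital-specific blocks, further strata, a counting error or a departure from the list could each be the cause, and the article does not allow a choice among them. The split calls for reconciliation. It is not by itself evidence of selection bias.

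**What to change.** 1. For the roughly 392 patients still to enrol, have the existing trial center generate a new list, stratified by hospital, with randomly varying block sizes that are not disclosed to sites. Amend the Randomization section to say that block sizes vary and are withheld. The cost is one new list and slightly looser balance within hospital.
2. Reconcile the 108 allocations, hospital by hospital, against the center's log: block size or sizes used, any further strata, order of entry, and arm of each of the eight excluded patients. Then correct the Randomization section or the reported numbers, whichever proves to be wrong. If a large block explains the split, a sentence saying so is enough. If there were departures from the list, document them and their cause. The cost is a one-off check of the log.

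Neither step changes any patient's care.

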### Time schedule

Patient recruitment will take place between 2006 and 2008. Between January and November 2006, each month approximately 15 patients were included in the MONET – study.

### Breast MRI

Breast MRI will be performed on a 3-T clinical MR system (Achieva, Philips, Best, The Netherlands). Patients will be placed in prone position. A dedicated phased-array bilateral breast coil (MRI devices, Würzburg, Germany) will be utilized for simultaneous imaging of both breasts. The scan protocol will include a transverse high-resolution T1-weighted fast gradient echo fat-suppressed series (TE/TR 1.7/4.5 msec; inversion delay SPAIR 130 msec; flip angle 10°; FOV 340 × 340 mm^2^, acquired voxel size 0.66 × 0.66 × 1.6 mm^3^, reconstructed voxel size 0.66 × 0.66 × 0.80 mm^3^) and a transverse T2-weighted fat suppressed spin echo series (TE/TR 120/9022 msec; inversion delay SPAIR 125 msec; flip angle 90°; FOV 340 × 340 mm^2^, acquired voxel size 1.01 × 1.31 × 2.0 mm^3^, reconstructed voxel size 0.66 × 0.66 × 2.00 mm^3^). Both series will be used to study the morphology of the lesion. A diffusion-weighted fat-suppressed series (TE/TR 61/5000 msec; inversion delay SPAIR 70 msec; flip angle 90 °; FOV 320 × 320 mm^2^; acquired voxel size 2.22 × 2.52 × 4.00 mm^3^, reconstructed voxel size 1.33 × 1.33 × 4.00 mm^3^; b-values 0, 150, 499 and 1500 seconds/mm^2^) will be acquired to assess the cellularity of the lesion. Finally, dynamic contrast-enhanced fat-suppressed T1-weighted gradient echo images (TE/TR 1.3/3.4 msec; flip angle 10°; FOV 320 × 320 mm^2^, acquired voxel size 0.91 × 0.91 × 2.00 mm^3^, reconstructed voxel size 0.83 × 0.83 × 1.00 mm^3^; dynamic scan duration 60 sec) will be acquired before and immediately after administration 0.1 mmol/kg Gadolinium-DTPA (Magnevist, Schering, Germany) to study the contrast enhancement of the lesions and herewith the perfusion of the lesion. All patients will receive this scan-package with a total scan duration of less than 30 minutes.

### Interpretation of Breast MRI

MR images of the breast will be interpreted on soft copy using a Picture Archiving and Communications System (PACS, Philips, Best, The Netherlands) that allows manual window level setting. MR images will be interpreted by two radiologists independently and in case of discrepancy, consensus will be sought. The radiologists will have access to the mammograms and ultrasound examination, but will be blinded for the results of the LCNB, following clinical practice. The MR images will be interpreted following the guidelines of the BI-RADS-MRI classification system proposed by the American College of Radiology [18]. Classification of the lesions will be based on lesion morphology, enhancement pattern and enhancement kinetics (persistent, plateau, or washout) [19,20]. Level of suspicion will be reported on a scale of 0 – 6: 0 additional imaging required; 1 normal; 2 benign; 3 probably benign, 6-month follow-up MRI recommended; 4 suspicious for malignancy; 5 highly suggestive of malignancy; 6 known malignancy.

### LCNB

LCNB will be performed under ultrasound guidance or stereotactically. A minimum of four 14 Gauge biopsy specimens per lesion is acquired. The histological diagnosis of the tissue sampled by means of the LCNB provides the definitive diagnosis. Based on histology, patient management will be planned: 'benign lesions' require mammographic follow-up, 'normal breast tissue' requires a repeat LCNB or open breast biopsy and in case of a 'high risk lesion' (i.e. lobular carcinoma in situ, atypical ductal or lobular hyperplasia), 'in-situ carcinoma' or 'invasive carcinoma' require image-guided needle localization followed by surgical excision with appropriate axillary staging (i.e. sentinel node biopsy or axillary lymph node dissection). Patient management will be the same for the MRI and the control group.

If in the intervention group an additional, mammographically occult lesion is detected on the MR images that requires tissue sampling, second-look ultrasound will be performed to determine whether the lesion is ultrasonographically evident and suitable for ultrasound-guided tissue sampling. If the lesion cannot be visualised by means of second-look ultrasound, MRI-guided large core needle biopsy will be performed.

